## Abstract

Supplemental Digital Content is available in the text

## Introduction

1

Type 2 diabetes mellitus results in high mortality and morbidity globally.^[1]^ The International Diabetes Federation estimates 75 million persons living with diabetes mellitus in India. Amongst them, 1.1 million adults (aged 20–79 years) die annually due to type 2 diabetes mellitus.^[2]^ Estimates also indicate around 42.2 million Indians currently living with undiagnosed type 2 diabetes mellitus.^[2]^ The total type 2 diabetes mellitus disorder burden in India is enormous, and the burden is set to increase if not managed. Hence, timely diagnosis/screening and management need to be scaled up in the country. The Indian Council of Medical Research has set forth guidelines for screening and management of type 2 diabetes.^[3]^

Most Indians (66.4% in 2017) live in the rural and semi-urban areas.^[4]^ They have limited access to healthcare facilities due to socio-economic status, distance, availability of facilities, inadequate number of skilled doctors, etc..^[5–10]^ Concurrently, the prevalence of type 2 diabetes mellitus is increasing in rural and semi-urban India. More individuals from the lower socio-economic status are now being identified with type 2 diabetes mellitus.^[11]^ Such persons with diabetes mellitus face catastrophic consequences. This is due to increasing type 2 diabetes mellitus burden and poor accessibility to public healthcare facilities. Hence, an innovative and feasible strategy is needed to improve access for efficient type 2 diabetes mellitus screening and management.

The use of minimally trained health workers in improving access to healthcare facilities has proven successful in low and middle-income countries.^[12–14]^ The successes have been observed for communicable and non-communicable diseases.^[15–26]^ Hence, type 2 diabetes mellitus screening and management by health workers in India offers a potentially feasible strategy. It can improve screening and subsequent management of type 2 diabetes mellitus and associated complications at the community level.

The Indian government in 2005, created a new cadre of non-physician minimally trained health volunteers. They are called accredited social health activists. These activists are female health volunteers. They are the primary interface between the public health care facilities and rural communities. They handle social mobilization and awareness in the 1000 residents of their community. Their primary activities include mobilizing women and children for reproductive and child health services, immunization of newborn, accompanying the referred cases for complications, etc. They are paid case-based incentives for her services.^[5,17]^ Currently, the government is also looking at utilizing the accredited social health activists’ services for non-communicable disease management.^[27]^ In lieu of the same, the government's National Program for prevention and control of Cancer, Diabetes, Cardiovascular diseases and Stroke has also formulated operational guidelines for the health workers^[28]^

Competence has been explained as the “*possession of requisite skills, knowledge, education and capacity*”.^[29]^ The competence about type 2 diabetes mellitus and its complications is a limiting factor in utilizing this workforce. It is important to provide standardized training to the health workers and then utilize their services in type 2 diabetes mellitus.^[18]^ Ultimately the training should improve the competency of the health workers to improve type 2 diabetes mellitus screening at the public healthcare facilities.

### Aim and objectives of the study

1.1

#### Aim

1.1.1

We aim to assess the effect of health worker training in improving their competence with respect to type 2 diabetes mellitus.

#### Objectives of the study

1.1.2

The following are the objectives:

a.To train the health workers in competency-based training for type 2 diabetes mellitus.b.To evaluate the training in realizing the change in the competence of the health workers.

### Primary hypothesis

1.2

We hypothesize that the competence levels of the health workers in the intervention package will increase the competence levels to 60% compared to an estimated level of 30% at the baseline.

## Methods

2

### Preliminary phase

2.1.1

This phase involves, identification of the study areas, the needs assessment with important stakeholders in these study areas and the designing and validation of the training module.

The training module will be collated using the modules developed by the Ministry of Health and Family Welfare, Government of India, The Indian Council of Medical Research, The National Program for Prevention and Control of Cancer, Diabetes, Cardiovascular diseases and Stroke, The Indian Institute of Public Health-Hyderabad and the Public Health Foundation of India will be utilized.^[3,30–32]^

Subsequently, a customized tool (questionnaire) will be developed for the evaluation of the competence, which will have both theoretical and practical components.

*Identification of Study area:* Eight health centers across Hyderabad & Ranga Reddy districts of the state of Telangana will be identified as the study sites. Caution will be exercised to ensure that the eight centers are spread widely across the district. It will ensure no contamination of health workers and their patients from the intervention to the control group or vice-versa. These centers will also be identified based on their consent and the availability of health workers*Needs Assessment:* A needs assessment exercise will be conducted involving the important stakeholders involved. The stakeholders will consist of government officials, the medical officer at the health center and the health workers from the cadre of workers to be trained.*Designing and Validation of Intervention package (training and evaluation tools):* The training module and evaluation questionnaires developed will be used for validating the entire intervention package at a neutral site with 10% of the calculated sample size, that is, 30 health workers. The questionnaire will be developed to assess the change in competence pertaining to type 2 diabetes mellitus and its associated complications after the training. Pre and post-test assessment using the questionnaire and practical tools will be conducted in the test population for validating the training and evaluation tool.

### Intervention phase

2.2

This phase will mainly consist of clustering of the health centers randomly into the intervention and control clusters, the identification and recruitment of health workers into the study based on the inclusion and exclusion criteria and the data collection procedure for training evaluation.

*Clustering of health centers:* This stage will entail the random division of the identified eight health centers into two clusters namely the intervention cluster and the control cluster.*Identification & Recruitment of Health Workers:* In this stage after the health centers have been randomized into the intervention and control clusters, the health workers will be screened for eligibility. Those eligible will be inducted into the study based on their consent. The selection will be dependent on the inclusion and exclusion criteria mentioned under study design. The participants will be explained about the process using a participant information sheet. (See document- Appendix 1 Supplemental Digital Content 1 (Appendix 1), which illustrates the Participant Information sheet). This sheet will be shared with each participant after translating it into their vernacular language.*Data Collection:* Using a baseline questionnaire, we will understand their competence in type 2 diabetes mellitus. This tool will be developed using Michigan University's Diabetes Knowledge Test-2,^[33,34]^ evaluation tools developed by the government of India and PHFI along with inputs from endocrinologists/physicians/public health experts. This will help us assess the baseline competence levels of the health workers. This tool will also capture the baseline data for the clinical competence of the participating health workers. All socio-demographic details and baseline details will be collected, entered and analyzed later.

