### Study design

2.3

We will conduct a 12 months prospective, unblinded, parallel cluster randomized controlled trial. The study will measure changes in healthcare worker competence levels related to type 2 diabetes mellitus and complications. The health centers chosen as the clusters will be then randomized into intervention and control arms. The health workers at the respective health center will be thus assigned to the respective cluster arm. The clusters will be chosen such that they are geographically distinct. This will avoid any possible contamination within the groups. Health workers in the control group will continue to deliver services according to the current standards and guidelines.^[28,30,31,35]^ The intervention group participants will undergo additional training. This will be spread over six months and delivered for 20 hours.^[36]^ It will entail pre and post-assessment questionnaires and practical assessments as the modality of evaluation.

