#### Sample size calculations

2.3.2

The sample size is calculated based on the following formulae: 

Where

 to two-tailed at 5% significance level = 1.96

 to 80% power = 0.84d = effect size (estimated) = 0.5 (medium effect based on Cohen's d)m = cluster size = 30 (minimum number of health workers at one health center)ρ = intracluster correlation coefficient (estimated) = 0.03

we get n as 117 HWs per group. Adjusting the same for a dropout rate of 20%, 

 we get n as 147 per cluster group, i.e. 294 HWs across both arms. Therefore, 294 HWs across 8 clusters will be needed with 37 HWs across each cluster arm. Each cluster has 40–45 health workers and hence the sample size calculated is feasible for the study.

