#### Sampling method

2.3.4

Cluster sampling method will be utilized for the study. First, 8 health centers will be chosen from the Hyderabad & Rangareddy districts and will further be then randomized as clusters into either the intervention or the control arms. All health workers at the respective clusters will be included in the respective arms based on their eligibility and consent.

A total of approximately 294 health workers will participate in the study, encouraged both by getting continuing education and by being urged by a district health officer to participate. We expect that approximately 147 health workers will enter the intervention arm, wherein they will participate in 20 hours of the intervention to be considered as trained. Evidence shows that even brief interventions have an impact on effective knowledge.^[36]^ The principal investigator and the field staff will take the requisite permission form authorities and enroll the participants into the study based on their consent, which will be recorded using a consent form.

To prevent possible confounding and effect modification of patients’ characteristics, we will divide the health centers into pairs. The pairs will have the following characteristics: male/female ratio, percentage of patients ≥ 60 years old, percentage of patients on treatment and the prevalence of patients suffering from chronic diseases. The centers will be then randomly allocated into an experimental group and a control group and will be compared to ascertain the balance of the allocation. This will be done using computer generated random number using the MS Excel software. Pre- and postassessment scores will be recorded at baseline and at after the intervention. These scores will serve as the data regarding competence assessment. Health workers’ characteristics will be not included in the randomization process. This data is not available prior to the information from the baseline questionnaire being received (Fig. 1 emphasizes the relationship, being examined in the evaluation). The intervention is randomized and is hence an important variable between exposure and outcome in the experimental group as well as the evaluation method (e.g., before and after study). Concurrently potential confounders will also be identified and would majorly consist of health workers’ characteristics.

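### Centres are randomised before workers are screened, consented and baseline-tested in an unblinded trial with no stated concealment, so consent and the baseline practical score can depend on the arm

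*Protocol article*

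**What the plan says.** Section 2.2 (Intervention phase) lists three steps in sequence.

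1. The eight centres are divided at random into intervention and control.
2. Workers are recruited: "after the health centers have been randomized into the intervention and control clusters, the health workers will be screened for eligibility", and then "Those eligible will be inducted into the study based on their consent".
3. Baseline data are collected: "Using a baseline questionnaire, we will understand their competence in type 2 diabetes mellitus". The same tool captures baseline clinical competence.

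Section 2.3.4 (Sampling method) is consistent with this order. It leaves worker characteristics out of the randomisation because "This data is not available prior to the information from the baseline questionnaire being received".

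On blinding, section 2.3 (Study design) says: "We will conduct a 12 months prospective, unblinded, parallel cluster randomized controlled trial".

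On who is enrolled, section 2.3.4 says: "All health workers at the respective clusters will be included in the respective arms based on their eligibility and consent". It describes the expected total of about 294 workers as "encouraged both by getting continuing education and by being urged by a district health officer to participate". Section 2.3.1 is worded more loosely and speaks of choosing a requisite number of workers who meet the inclusion criteria. Section 2.3.2 derives 37 workers per centre and adds: "Each cluster has 40–45 health workers and hence the sample size calculated is feasible for the study".

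On the baseline score, section 2.4.3 combines a paper and a practical test and has the same experts run the practical test before and after training. Section 2.5 brings baseline values into a linear mixed model.

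**The concern.** Randomising centres balances, in expectation, the workers attached to those centres. It does not balance the workers who agree to take part if they agree after the arm is settled and may be known. Unwilling workers are excluded (section 2.3.3), and what a worker agrees to differs by arm: testing alone in control, testing plus 20 hours of training over six months in intervention. The two groups of volunteers could then differ in motivation or prior competence for reasons unrelated to the training.

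The second route is the baseline measurement. Competence is judged as a change from baseline. If an assessor who knows the arm marks the baseline practical test differently in one arm, the error enters the estimated effect directly. Neither problem can be repaired once recruitment and baseline testing are over.

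**Working it through.** **Order and concealment.** Section 2.2 puts randomisation first, screening and consent second, baseline third. Section 2.3.4 agrees. Section 2.3 says unblinded. No section says that the allocation is withheld from anyone until enrolment and baseline are complete. The article does not state outright that workers or assessors are told the arm; that they can know it follows from these three facts together.

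**How exposed the baseline practical score is.** Section 2.4.1 assigns the practical evaluation to a neutral doctor and makes the mechanism identical in both arms. Sections 2.4.2 and 2.4.3 assign it to a fixed set of public health experts, and 2.4.3 promises objective parameters. Section 3.2 calls the practical evaluations subjective. None of these says the assessor is masked.

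**The plan's own sample size, reproduced.** Inputs from section 2.3.2: z values 1.96 and 0.84, d = 0.5, m = 30, intracluster correlation 0.03, dropout 20%.
- Unclustered n per arm = 2 × (1.96 + 0.84)² / 0.5² = 62.72
- Design effect = 1 + (30 − 1) × 0.03 = 1.87
- n per arm = 62.72 × 1.87 = 117.3 (stated: 117)
- With dropout: 117 / 0.8 = 146.25, rounded up to 147; × 2 = 294; / 8 = 36.75, rounded up to 37 per centre

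The stated figures reproduce.

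**Standard error in SD units.** √(2 × 1.87 / 117) = 0.179.

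**Illustrative size of a recruitment bias.** The documents give no refusal rate, so these are assumptions.
- Non-participation: if a centre with 40 to 45 workers enrolled just the 37 it needs, 1 − 37/40 = 7.5% to 1 − 37/45 = 17.8% would be missing. The plan does not say this will happen; it only sets a scale.
- Assume the loss occurs in one arm only and that missing workers differ from enrolled ones by 0.5 to 1 SD.
- Shift in that arm's mean = fraction missing × difference: 0.075 × 0.5 = 0.04 SD to 0.178 × 1 = 0.18 SD, or about 7% to 36% of d = 0.5.
- Cross-check by another assumption: with a correlation of 0.1 to 0.5 between willingness and competence, the shift is about 0.02 to 0.16 SD.

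**Effect on the 5% error.** With no true effect and residual bias b, the two-sided rate is P(Z > 1.96 − b/0.179) + P(Z < −1.96 − b/0.179).

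| b (SD) | rate |
|---|---|
| 0.04 (0.0375 unrounded) | about 5.5% |
| 0.10 | about 8.7% |
| 0.18 | about 17% |

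**What baseline adjustment does.** A true baseline difference between arms is removed to the extent that the baseline score captures it. A scoring error does not behave that way. If the baseline is marked e too low in one arm, a change-score comparison moves by e in that arm's favour, and a model with baseline as covariate (slope β) moves by β × e. Adjustment then carries the error into the effect.

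**The case against.** Several points on the other side stand.

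- The article never says that staff or workers know the arm at consent or baseline. A reader might infer it as fact; the documents support only that nothing prevents it.
- A reader might infer that the inducement of continuing education exists only in the intervention arm. Section 2.3.4 applies it, and the urging by a district officer, to the whole expected total of about 294. The urging would tend to reduce refusal in both arms. What differs by arm on the page is the additional training, which makes a different appeal plausible but does not prove it.
- A reader might take 37 needed out of 40 to 45 available as room to hand-pick workers. Section 2.3.4 enrols all who are eligible and consent, the criteria are few and mostly objective, and 37 is a derived requirement used to show feasibility, not a quota. Section 2.3.1 is looser but does not override this.
- A reader might assume that the bias favours the intervention. The training is also a burden, so refusals could run either way, and more motivated workers with high baseline scores have less room to gain.
- The 17% figure is the worst corner of the assumed inputs, taken before any baseline adjustment. Similar shortfalls in both arms would give no bias.
- The paper test is less exposed than the practical test, and the neutral doctor and identical procedures help. Neutral is not masked, however, and section 3.2 concedes subjectivity.

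These points limit the size and certainty of the problem. They do not change the stated order or supply concealment.

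**Conclusion.** The concern holds in a limited form. Followed as written, the plan leaves two things open to knowledge of the arm: the decision to consent, and the baseline practical score. Direction and size are not established by the documents. The range of 0.04 to 0.18 SD, and the error rate of about 5.5% to 17%, rest on one-sided non-participation of 7.5% to 17.8%, an assumed difference of 0.5 to 1 SD, the plan's own design effect of 1.87 with 117 per arm, and no baseline adjustment. The documents do not show that the comparison is invalid. This is an avoidable weakness in the sequence of steps, worth correcting before recruitment because the correction is cheap and cannot be made afterwards.

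**What to change.** Reorder section 2.2. In all eight identified centres, screen every eligible worker, obtain consent, and complete the paper and practical baseline tests; only then randomise the paired centres. If the allocation must be drawn earlier, state that it is withheld from workers, recruiters and baseline assessors until those steps are complete.

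Keep the rule in section 2.3.4 that all eligible, consenting workers are enrolled, and bring the wording of section 2.3.1 into line with it.

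The change is feasible as planned: the centres are identified in the preliminary phase, the pairing uses centre-level patient characteristics, and both arms use the same evaluation tools. The cost is resequencing and a short delay between baseline and the start of training. No extra staff or tests are needed, and 117, 147 and 294 stand. The change does not address unblinded assessment after training or differential dropout.

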### Study design

2.3

We will conduct a 12 months prospective, unblinded, parallel cluster randomized controlled trial. The study will measure changes in healthcare worker competence levels related to type 2 diabetes mellitus and complications. The health centers chosen as the clusters will be then randomized into intervention and control arms. The health workers at the respective health center will be thus assigned to the respective cluster arm. The clusters will be chosen such that they are geographically distinct. This will avoid any possible contamination within the groups. Health workers in the control group will continue to deliver services according to the current standards and guidelines.^[28,30,31,35]^ The intervention group participants will undergo additional training. This will be spread over six months and delivered for 20 hours.^[36]^ It will entail pre and post-assessment questionnaires and practical assessments as the modality of evaluation.

#### Population, sample, and setting

2.3.1

Our target population will be health workers working in chosen health centers of Hyderabad & Rangareddy districts of Telangana. The requisite number of health workers (See document- Appendix 2, Supplemental Digital Content (Appendix 2), which illustrates the probable sites of study) will be chosen upon satisfying the inclusion criteria mentioned later.

#### Sample size calculations

2.3.2

The sample size is calculated based on the following formulae: 

Where

 to two-tailed at 5% significance level = 1.96

 to 80% power = 0.84d = effect size (estimated) = 0.5 (medium effect based on Cohen's d)m = cluster size = 30 (minimum number of health workers at one health center)ρ = intracluster correlation coefficient (estimated) = 0.03

we get n as 117 HWs per group. Adjusting the same for a dropout rate of 20%, 

 we get n as 147 per cluster group, i.e. 294 HWs across both arms. Therefore, 294 HWs across 8 clusters will be needed with 37 HWs across each cluster arm. Each cluster has 40–45 health workers and hence the sample size calculated is feasible for the study.

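### The sample-size calculation does not support 80% power for d = 0.5: it uses normal quantiles with only 8 randomised centres, and on 6 df the plan's own inputs give about 65% without baseline adjustment

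*Protocol article*

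**What the plan says.** Section 2.3.2 of the protocol article lists the inputs: a quantile given as "to two-tailed at 5% significance level = 1.96", 0.84 for 80% power, a medium standardised effect (d) of 0.5, a cluster size of 30, and "intracluster correlation coefficient (estimated) = 0.03". From these, "we get n as 117 HWs per group". Allowing for 20% dropout gives 147 per arm, and the section ends: "294 HWs across 8 clusters will be needed with 37 HWs across each cluster arm". It adds that each centre has 40 to 45 workers.

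Sections 2.3 and 2.3.4 make the health centre the unit of randomisation. Before allocation, "we will divide the health centers into pairs". Section 2.5 names a linear mixed model that takes in baseline values, with a random effect for the participant over time.

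**The concern.** The design effect enlarges the variance to allow for correlation within centres. It does not allow for the between-centre variance being estimated from very few centres. With 8 centres the reference distribution for the arm comparison is a t with few degrees of freedom, and 1.96 is too small a critical value for a 5% test. The text of 2.3.2 has no small-cluster allowance: no t quantile and no added centres.

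At stake is how the result is read. If the chance of missing d = 0.5 is nearer 35% than 20%, a non-significant result is weaker evidence against a medium-sized effect than the published calculation suggests.

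**Working it through.** **Inputs (all from 2.3.2 unless noted).** Two-sided alpha 5%; power 80%; d = 0.5 in SD units; m = 30; ICC 0.03; dropout 20%; 8 centres. Four centres per arm is inferred from 147/37 = 3.97 and from the pairing in 2.3.4. The article does not state it outright.

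**1. Reproduce the plan's figures.** The formula itself is lost from the extracted text, but the listed inputs fit the usual design-effect formula:

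- Without clustering: 2 × (1.96 + 0.84)² / 0.5² = 2 × 7.84 / 0.25 = 62.72 per arm.
- Design effect: 1 + (30 − 1) × 0.03 = 1.87.
- Clustered: 62.72 × 1.87 = 117.3, given as 117.
- Dropout: 117.3 / 0.8 = 146.6, given as 147, so 294 in all.

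Both stated figures are reproduced. No sum is wrong.

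**2. Power with the degrees of freedom the design has.** With 117 analysable per arm in 4 centres, the mean centre size is 117/4 = 29.25.

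- Design effect: 1 + 28.25 × 0.03 = 1.8475.
- Standard error of the difference: √(2 × 1.8475 / 117) = 0.1777.
- Non-centrality: 0.5 / 0.1777 = 2.81.
- Degrees of freedom: 2 × (4 − 1) = 6; critical value 2.447.

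| Reference distribution | Critical value | Power for d = 0.5 |
|---|---|---|
| Normal (as in the plan) | 1.96 | 80.3% |
| t, 6 df | 2.447 | 65.2% |

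On 6 df, the effect detectable with 80% power is d = 0.60.

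**3. Does a larger number analysed rescue it?** (6 df, ICC 0.03)

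| Analysed per arm | Basis | Power |
|---|---|---|
| 117 | plan, after dropout | 65% |
| 147 | plan, no dropout | 70% |
| 160 | 40 at each of 4 centres, no dropout | 72% |
| 180 | 45 at each of 4 centres, no dropout | 74% |

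No. The limit is the number of centres.

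**4. Sensitivity to the ICC** (6 df, 117 per arm, no baseline adjustment)

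| ICC | 0.01 | 0.03 | 0.05 | 0.10 |
|---|---|---|---|---|
| Power | 80% | 65% | 54% | 38% |

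**5. Sensitivity to baseline adjustment** (6 df, 117 per arm, ICC 0.03). The baseline-outcome correlation r is an assumption, since the article gives none. The variance is multiplied by 1 − r² at both the worker and the centre level.

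| r | 0 | 0.5 | 0.55 | 0.6 | 0.7 |
|---|---|---|---|---|---|
| Power | 65% | 77% | 80% | 83% | 90% |

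**6. Sensitivity to a pair-level analysis.** Four pairs leave 3 df (critical value 3.182). If matching removes no between-centre variance, power is 48.6%.

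**7. Keeping 1.96 as the critical value.** A t on 6 df exceeds 1.96 in absolute value with probability 9.8%, so nominal power near 80% would be bought with about twice the stated type I error.

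**The case against.** The strongest reply is that 65% describes an unadjusted comparison of post-training scores, whereas 2.5 plans a model that takes in baseline values, and both arms are assessed at baseline. This stands in part. A correlation of about 0.55 would bring power on 6 df back to 80%, so a reader should not infer that the trial itself cannot reach 80%. What is shown is narrower: the published calculation does not deliver it, because 2.3.2 neither states nor uses such a correlation.

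A second reply is that an ICC of 0.01 also gives 80%. That is true, but the plan chose 0.03, and less favourable values are equally open.

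A harsher reading is also tempting: that the pairing cuts power to about 49%. The article does not support this as a headline. Section 2.5 specifies no pair term or pair-level test, 2.3.4 does not say explicitly that allocation is made within pairs, and the figure assumes that matching gains nothing. It belongs in a sensitivity note.

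Nor is this an arithmetic error, since 117 and 147 follow from the inputs. And it is not a detail that a separate analysis plan could settle: the quantiles, the number of centres and the power claim all stand in the article and do not fit together.

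**Conclusion.** The point holds as a mismatch of method. The 80% power stated for d = 0.5 is not supported by a calculation that uses normal quantiles for 8 randomised centres. Under the plan's own inputs the shortfall is about 15 percentage points (65% against 80%), or about 10 if nobody drops out. These figures assume 4 equal centres per arm, ICC 0.03, a valid test on 6 df and no baseline adjustment. The true power of the planned model may be higher, by an amount the article gives no basis for stating.

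**What to change.** Keep 8 centres and 294 workers, and replace the power statement in 2.3.2 with wording such as: *With 4 centres per arm, t on 6 df, ICC 0.03 and no baseline adjustment, 294 recruited workers (about 234 analysable after 20% dropout) give about 65% power for d = 0.5 and 80% power for d of about 0.60.*

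The figure must be tied to the 234 analysable (2 × 117), not to the 294 recruited, because analysing all 294 gives about 70%.

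Add the table of unadjusted power over ICC 0.01 to 0.10. Keep a claim of 80% for d = 0.5 only if the text states and justifies a baseline-outcome correlation (about 0.55 or more, assuming equal variance reduction at both levels) and says that the test uses small-sample degrees of freedom. If a pair-level analysis is intended, say so and report its power on 3 df.

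The cost is rewording and one small table. Recruitment, centres and procedures do not change, but a published figure becomes less favourable.
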